### Objectives

The primary objective of the BEST trial is to determine the effect of resistance training on fatigue compared to a relaxation control group among breast cancer patients during adjuvant radiotherapy.

Secondary objectives are to estimate the effects of the resistance training on quality of life, depression, cognitive function, and early and late radiotoxicity, as well as on physical fitness, including muscle strength, cardio-respiratory fitness, flexibility, and body composition. The effects of the resistance training on immunologic and inflammatory parameters and other biomarkers relevant to cancer prognosis will also be tested. Further, hypothesized biological mediators of physical activity and cancer-related fatigue will be explored and the relationships between cancer-related fatigue, physical fitness, and biomarkers of stress, inflammation, and immune function will be modelled. Safety and feasibility of progressive resistance training during radiotherapy will be evaluated, and the sustainability of the effects will be assessed.

### Patient selection

The BEST study includes women with histologically confirmed primary breast cancer who are scheduled for adjuvant radiotherapy at the University of Heidelberg Medical Center and who do not have any contraindications for a progressive resistance training. Inclusion and exclusion criteria are provided in Table 1.

**Table 1 T1:** Inclusion and exclusion criteria of the BEST study

**Inclusion criteria**	**Exclusion criteria**
• Female patients with histologically confirmed primary breast cancer, stage I-III after lumpectomy or mastectomy scheduled for adjuvant radiotherapy at the University of Heidelberg Medical Center	• Acute infectious disease
	• Inability to walk or stand
	• Severe neurological deficiencies
• Age ≥18 years of age	• Severe cardiac or cardiovascular disease
• BMI ≥18 kg/m^2^	• Severe respiratory insufficiency
• Ability to understand and follow the study protocol	• Severe renal failure
• Willingness to come to the Heidelberg exercise facilities and adhere to study protocol	• Other concurrent malignant disease (except carcinoma in situ of skin or cervix)
• Written informed consent	• Substance abuse (potentially leading to non-compliance)
	• Participation in systematic intense resistance or aerobic training (at least 1 h twice per week)
	• Previous participation in another exercise intervention trial

### Recruitment and randomization

All eligible breast cancer patients scheduled for adjuvant radiotherapy at the University of Heidelberg Medical Center are briefly informed about the BEST study during the therapy counselling visit (about 1-2 weeks before start of radiation). If interested, patients are then informed in detail by the BEST study physician and inclusion and exclusion criteria are verified. For each patient recruited into the study, written informed consent is essential prior to inclusion into the study after extensive information about the intent of the study, the study regimen, potential associated risks and side effects. The investigator will not undertake any diagnostic measures specifically required for the clinical trial until valid consent has been obtained. Upon written informed consent, the patient is scheduled for the baseline visit, which should be within 21 days prior to the start of radiation.

After completion of the baseline assessment and if the testing procedure does not indicate cardiovascular, respiratory or neurological problems that may contraindicate resistance training, the participant is randomly allocated to one of the two intervention groups. Allocation is done by the biometrician based on a predetermined list generated with a blocked randomization SAS procedure with a fixed block size, stratified by age (< 50 / ≥ 50 years of age) and baseline physical fatigue level (< 14 / ≥ 14). Stratification is used in the randomization process, as we anticipate these variables to have major influence on the outcome. To prevent possible bias, study personnel involved in the recruitment and the baseline assessment do not have access to the randomization lists and are not aware of the block size. Conversely, the biometrician does not have influence on the recruitment procedure.

Recruitment of n=160 patients started in February 2011 and was completed in March 2013.

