#### Fatigue

The primary endpoint is change of fatigue from baseline to week 13. Fatigue is assessed with the Fatigue Assessment Questionnaire (FAQ) which is a 20-item, multidimensional self-assessment questionnaire that has been validated for a German-speaking population [42]. It covers the physical, affective, and cognitive fatigue dimensions, and includes one item on sleep disorders. Scores are derived by summing the answers (0=not at all, 1=a little, 2=quite a bit, 3=very much) of the appropriate items. Reference values of the FAQ scores are available from a representative sample of the German population including 1,340 women stratified by age [43].

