### Sample size

The primary aim is to compare changes on the overall fatigue scale from baseline to week 13 between the exercise and relaxation group. To detect a mean standardized effect size of 0.5 with a two-sided t-test with significance level 0.05 with a power of 80% a sample size of 80 breast cancer patients per arm is needed, 160 women in total, assuming a maximal drop-out rate of 20%. However, adjustment for the pre-intervention fatigue value in the regression models on post-intervention fatigue will lead to an improved power above 80% depending on the correlation between the pre- and post-intervention values [60].

This sample is also large enough to detect medium sized clinically relevant intervention effects on the secondary outcome EORTC QLQ-C30 subscales. Evidence-based guidelines for the interpretation of the clinical relevance of changes in the different EORTC QLQ-C30 subscales were recently published [48], categorizing difference between scores (on the 0-100 points scale) in trivial, small, medium, or large effect sizes. For example, effects are considered as medium size for differences of 19-29 in role function, differences of 14-22 in physical function, 11-15 in social function, 9-14 in cognitive function, and 13-19 for fatigue.

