### Data analysis

The main intervention effect will be assessed on the basis of a comparison between exercisers and controls as defined at randomization, regardless of exercise adherence, i.e. according to the intent-to-treat principle. The differences in fatigue between groups will be assessed with a generalized estimating equation (GEE), which accounts for repeated observations on the same subjects over time. This method provides the most efficient estimate for the intervention effect in pretest-posttest trials [61]. Normality assumptions will be checked and data if necessary transformed. Imputation-based sensitivity analyses will be conducted to examine the potential effect of missing data on the results.

Similar analyses as for fatigue will also be performed for the secondary endpoints. In addition, analyses will be performed stratified by pre-treatment (e.g. neoadjuvant, adjuvant or no previous chemotherapy), to evaluate potential differential effects of the exercise intervention by pre-treatment. Further, subgroup effects of resistance training versus relaxation controls will be explored stratified by training adherence, changes in muscle strength, cardiorespiratory fitness, and body composition. Correlation analyses will be used to examine the relationship between changes of the various measured endpoints. Regression analyses regarding the repeated measurement design (T0, T1, T2, T3, T4, T5) will be applied to investigate the association between therapy modalities, cardiorespiratory fitness, muscle strength, and body composition and the different fatigue as well as QoL dimensions. The influence of other potential confounding factors, such as age, smoking, clinicopathologic characteristics, and comorbidities will be explored and accounted for in the analyses.

In addition, change in physical activity behavior post intervention will be explored for the follow-up time points using descriptive analysis.

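### The factors used to stratify randomisation are not fixed terms in the stated analysis model, and age is left to an open list of confounders; the cost is modest and conservative

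*Protocol article*

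**What the plan says.** **Design.** Under Recruitment and randomization, allocation is in blocks, "stratified by age (< 50 / ≥ 50 years of age) and baseline physical fatigue level (< 14 / ≥ 14"). The stated reason: "Stratification is used in the randomization process, as we anticipate these variables to have major influence on the outcome".

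**Endpoint.** Sample size: "The primary aim is to compare changes on the overall fatigue scale from baseline to week 13", compared between the two arms. The questionnaire is multidimensional; the Fatigue subsection says: "It covers the physical, affective, and cognitive fatigue dimensions, and includes one item on sleep disorders". The stratum therefore uses one dimension of the instrument, and the endpoint uses the overall score.

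**Model.** Data analysis names a GEE for the group difference in fatigue and gives no covariates with it. It extends similar analyses to the secondary endpoints. The one commitment on covariates for the treatment comparison stands in Sample size: "adjustment for the pre-intervention fatigue value in the regression models on post-intervention fatigue will lead to an improved power above 80" per cent.

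**Age.** Its only appearance in the analysis text is: "The influence of other potential confounding factors, such as age, smoking, clinicopathologic characteristics, and comorbidities will be explored and accounted for in the analyses".

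**The concern.** Balancing the arms on a prognostic factor removes that factor's contribution to the true variability of the treatment estimate. A model that omits the factor still counts its contribution as noise. The reported standard error is then too large, the test rejects too rarely under the null, and some precision gained by stratifying goes unused.

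There is also a question of pre-specification. At the design stage age was judged important enough to stratify on. At the analysis stage it sits with smoking and comorbidities in a list that is explicitly not closed. If that list bears on the treatment comparison, more than one adjusted estimate is compatible with the text. If it does not, age has no stated place in that comparison. Either way the role of a design factor in the main result is not settled in this document.

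**Working it through.** **1. The plan's own figure.** Inputs from Sample size: standardised effect d = 0.5, two-sided 0.05, power 80%, drop-out 20%. A two-sample t-test (noncentral t) with 64 per arm has power 0.801, and 64/(1 − 0.20) = 80 per arm. The stated 160 in total reproduces.

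**2. Which factor is really left out.** The primary model carries pre-intervention fatigue according to Sample size. To see whether the fatigue stratum adds anything to that, trials were simulated under the null with 128 evaluable women, four strata and 6,000 trials per scenario, using a linear model for the post-intervention value. Assumptions, none of them from the documents: blocks of 4, pre-post correlation 0.5, correlation 0.85 between physical and overall baseline fatigue, 70% aged 50 or over. The Monte Carlo error of a type I error near 0.05 is √(0.05 × 0.95/6000) ≈ 0.003.

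| Age share of residual variance | Baseline only: type I, mean CI width | Baseline + both strata: type I, mean CI width |
|---|---|---|
| 0 | 0.050, 0.606 | 0.050, 0.607 |
| 2% | 0.043, 0.607 | 0.045, 0.602 |
| 5% | 0.043, 0.607 | 0.049, 0.592 |
| 10% | 0.038, 0.607 | 0.048, 0.577 |

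With no age effect, adding the strata to a model that already holds baseline fatigue changes nothing of note. The gain in the lower rows comes from age.

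**3. Size of the age effect.** Let R² be the share of residual variance explained by the age stratum, after baseline fatigue. The documents give no value, so a range is assumed.

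- Excess CI width if omitted: 1/√(1 − R²) − 1
- Type I error if omitted: 2 × [1 − Φ(1.96/√(1 − R²))]
- Power if included: t-test power at effect 0.5/√(1 − R²), 64 per arm

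| R² (assumed) | Excess width | Type I error | Power with age included |
|---|---|---|---|
| 0 | 0% | 0.050 | 0.801 |
| 1% | 0.5% | 0.049 | 0.805 |
| 2% | 1.0% | 0.048 | 0.809 |
| 5% | 2.6% | 0.044 | 0.821 |
| 10% | 5.4% | 0.039 | 0.841 |

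The simulated widths agree: 0.607/0.577 = 1.052 at 10%.

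**4. Reading the power column.** The benchmark 0.801 is the planning value. With stratified allocation and age omitted, actual power is slightly higher, because the estimate varies less than its standard error says: Φ[(0.5 × √32 − 1.979)/√(1 − R²)] = Φ(0.849/0.995) ≈ 0.803 at 1% and Φ(0.849/0.949) ≈ 0.815 at 10%. The loss due to omission alone is therefore about 0.2 to 2.6 percentage points. These figures take d = 0.5 relative to the SD before age is added and leave out the gain from baseline fatigue. At a correlation of 0.5 that gain alone takes power from 0.801 to 0.900.

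**The case against.** Three stronger readings are tempting, and the document does not support them.

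- *Both factors are outside the model.* The Sample size section commits to adjusting for pre-intervention fatigue, and physical fatigue is a dimension of that questionnaire. For the primary endpoint the fatigue factor is largely covered.
- *Standard errors are 5% to 20% too wide, with type I error of 3.9% down to 1.9%.* Those values assume that the strata explain 10% to 30% of the variance and that the model has no covariates. In the simulation above, a covariate-free model did give intervals about 15% too wide (0.698/0.607), but the article does not propose that model.
- *Covariates will be picked by their effect on the result.* The text describes no such selection. It says that the factors will be allowed for, and age is the first one named.

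It can also be said that the confounder sentence closes a paragraph on secondary endpoints, subgroups and association models, so it may not govern the randomised comparison at all. This is a fair reading, but age then has no stated role in the primary model. Finally, this is a condensed article, and a covariate list commonly belongs to the full protocol or SAP. That would answer a complaint about silence. Here, however, the article does address age, and its open list sits badly with the reason given for stratifying. Any error is conservative, and balance between the arms holds under any model.

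**Conclusion.** The point holds in a limited form. Neither stratum is named as a fixed term, and a factor expected at design to matter strongly is left to an open list at analysis. For the primary endpoint the loss comes mainly from age: an interval about 0.5% to 5% too wide and a type I error of about 0.049 to 0.039, if age explains an assumed 1% to 10% of residual variance; nil if it explains none. These sizes rest on that assumed range and on baseline fatigue being in the model as Sample size says. For the secondary endpoints, neither the baseline value nor a stratum is named, and their size cannot be worked out from the document. There is no inflation of false positives, no bias in the randomised comparison and no effect on the 80 per arm. Settling the covariates in advance matters at least as much as the precision.

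**What to change.** In the Data analysis section, state that the primary model and the secondary-endpoint models include, as fixed covariates, the baseline value of the endpoint and both stratification factors as used at randomisation (age below 50 or not, baseline physical fatigue below 14 or not). Confine adjustment for smoking, clinicopathologic characteristics and comorbidities to a sensitivity analysis with a covariate list named in advance. If the SAP already fixes this, bring the two texts into line.

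The cost is one or two sentences and two degrees of freedom. In the simulation, when age had no effect, this changed the mean interval width only from 0.606 to 0.607. Both factors were recorded before allocation, so no new data are needed and the sample size stands.

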### Interventions

The begin of the training is the day of the first radiotherapy treatment. Patients participate in the intervention or control program for 60 minutes, twice weekly for 12 weeks. Participants train together with other cancer patients under supervision and guidance of experienced therapists. At days of radiation, participants frequently train directly before or after radiation due to logistic reasons. The physical status and well-being prior to and after a training session are recorded by the participant. The trainer documents attendance of each participant at each session. Similarly, if sessions have been missed, reasons are documented. In addition, for the resistance training individual weights and number of repetitions performed are documented.

#### Exercise intervention

Sessions are comprised of machine-based resistance exercise located at the training center of the Institute for Sports and Sports Sciences in Heidelberg. The hypothetical one-repetition maxima (1-RM) according to the Brzycki-Method [39] is defined for each exercise task in the first training session. The resistance training protocol complies with the American College of Sports Medicine (ACSM) exercise guidelines for cancer survivors [12] and with ACSM recommendations for progressive resistance training for novice weightlifters and older adults. This protocol includes one to three sets at a weight that can be handled for 8 to 12 repetitions (approximately 60–80% of 1-RM) [40,41] with a resting time of one minute between the sets. A complete session takes approximately 60 minutes and includes eight different types of exercises for major upper and lower muscle groups: 1) leg extension; 2) leg curl; 3) leg press; 4) shoulder internal and external rotation; 5) seated row; 6) latissimus pull down; 7) shoulder flexion and extension; and 8) butterfly and butterfly reverse. Training is progressive in terms of weight increase to the next machine weight level (at least by 5%) after successfully completing 3 sets of an exercise with 12 repetitions in three consecutive exercise sessions.

#### Relaxation intervention

Similar to the resistance training the relaxation intervention is performed for 60 minutes, twice weekly for 12 weeks in the exercise facility of the National Center for Tumor Diseases (NCT) in Heidelberg. It is based on the progressive muscle relaxation method according to Jacobson and does not include any aerobic or muscle strengthening components [37].

### Outcome measures

The outcome measures used in the BEST study are summarized in Table 2.

**Table 2 T2:** Assessments and instruments used in the BEST study

**Outcomes**	**Instrument**	**T0**	**T1**	**T2**	**T3**	**T4**	**T5**
**Primary endpoint**							
Fatigue	Fatigue assessment questionnaire (FAQ)	X	X	X	X	X	X
**Secondary endpoints**							
Quality of life	EORTC QLQ30 / BR-23 questionnaire	X	X	X	X	X	X
Depression	Center for Epidemiological Studies Depression Scale (CES-D)	X	X	X	X	X	X
Cognitive function	Trail-making-test	X	X	X		X	X
Body composition	Bioimpedance analysis, weight, height, waist and hip circumference	X	X	X		X	X
Muscle strength	Isometric and isokinetic strength of representative muscle groups for upper and lower extremity measured at the IsoMed2000®	X		X		X	X
Cardio-respiratory fitness	Spiroergometry (VO2peak)	X		X		X	X
Flexibility	Range of motion measured at the IsoMed2000®	X		X		X	X
Radiotoxicity	Acute radiation dermatitis, LENT-SOMA classification for late effects, ECOG performance status, hemoglobin , and thrombocytes at end of radiotherapy		X	X			
Circulating immune cells	Analyzed in peripheral blood	X	X	X			
Biomarkers of inflammation and oxidative stress	Analyzed in peripheral blood and urine	X	X	X			
Salivary cortisol	Saliva collected at five different time points during a day	X	X	X			
Sample collection data	Date and time of collection, as well as time since last food or fluid intake, vigorous physical activity (during last 12 h), NSAID intake (during last 12 h), smoking (during last 24 h), caffeine intake (during last 6 h), alcohol intake (last 48 h), acute infections, and sleep quality during last night are recorded.	X	X	X			
Safety of training interventions	Number of participants with lymphedema, pain, nausea, dyspnea, or tachycardia during the intervention phase	at each training session					
**Others**							
Socio-demographic factors	Recording of date of birth, education, occupation, socio-familial situation, smoking, alcohol consumption	X					
Breast cancer characteristics	Family history, TNM status, grading, ER/PR status, HER2-score, p53, bcl-2, Ki-67,	X					
Medical history	Recording of pre-existing diseases and of allergies	X					
Treatment data	Pre-treatment: ECOG at diagnosis, date and type of breast surgery, affected lymph nodes, (neo-) adjuvant chemotherapy (type, last infusion), hormone therapy		X				
	Radiation: technique (3D, IMRT), type and dose, start and stop date, interruptions						
Concomitant medication	Recorded at each visit on a medication log form	X	X	X			
Physical activity history	Physical activity in adolescence, pre-diagnosis, during, and after intervention is recorded, including walking, cycling, and sports	X		X	X	X	X

#### Fatigue

The primary endpoint is change of fatigue from baseline to week 13. Fatigue is assessed with the Fatigue Assessment Questionnaire (FAQ) which is a 20-item, multidimensional self-assessment questionnaire that has been validated for a German-speaking population [42]. It covers the physical, affective, and cognitive fatigue dimensions, and includes one item on sleep disorders. Scores are derived by summing the answers (0=not at all, 1=a little, 2=quite a bit, 3=very much) of the appropriate items. Reference values of the FAQ scores are available from a representative sample of the German population including 1,340 women stratified by age [43].

#### Quality of life (QoL)

QoL is assessed with the validated 30-item self-assessment questionnaire of the European Organisation for Research and Treatment of Cancer (EORTC QLQ-C30, version 3.0). It includes five multi-item functional scales (physical, role, emotional, cognitive, and social function), three multi-item symptom scales (fatigue, pain, nausea/vomiting), and six single items assessing further symptoms (dyspnea, insomnia, appetite loss, constipation, diarrhea) and financial difficulties [44]. In addition, the 23-item breast cancer specific module (EORTC QLQ-BR23) is applied, assessing common problems of breast cancer patients, e.g. with the affected breast or arm. Scores are derived according to the EORTC scoring manual [45]. Reference values are available from the EORTC reference manual [46] and from a sample of the general German population stratified by gender and age [47]. Further, evidence-based guidelines for the interpretation of the clinical relevance of changes in the different EORTC QLQ-C30 subscales were recently published [48], categorizing differences between scores in trivial, small, medium, or large effect sizes.

#### Depression

Depressive symptoms are assessed with the 20-item Center for Epidemiological Studies Depression Scale (CES-D). The CES-D scale is a widely used validated self-report instrument to measure current depressive symptomatology and to identify possible cases of depressive disorders, both in the general population and in patients with cancer [49].

#### Cognitive function

Cognitive function (concentration, cognitive flexibility) is estimated with the trail-making-test. This is a standardized, reliable and valid measure used in neuropsychological diagnostics [50,51]. The test measures the time needed by the participant to connect numbers and letters on a sheet of paper in a logical sequence.

